## The M-SKIP project: rationale and aims

Melanocortin-1-receptor (*MC1R*, MIM#155555) is one of the major genes that determine skin pigmentation and it has been reported to be associated with risk of melanoma [14], possibly through the determination of the tanning response of skin to UV radiation [15-17]. However the relationship between some *MC1R* variants and melanoma also in darkly-pigmented European populations suggests that *MC1R* signaling may have an additional role in skin carcinogenesis beyond the UV-filtering differences between dark and fair skin [18]. In previous meta-analyses [14,19,20] authors found evidence of a significant association between melanoma, red hair and fair skin and the five *MC1R* variants R151C, R160W, D294H, D84E and R142H, and suggested a possible role in melanoma development, via non-pigmentary pathways, for I155T and R163Q variants. However, the specific contribution of each *MC1R* variant to melanoma development via pigmentary and non-pigmentary pathways could not be evaluated in meta-analyses due to the lack of individually joint information on *MC1R* variants and phenotypic characteristics.

The aim of the M-SKIP project is therefore to perform a pooled-analysis of individual data on sporadic skin cancer cases and controls with information on *MC1R* variants, in order to: 1) assess the association of *MC1R* variants with melanoma, basal cell carcinoma (BCC) and squamous cell carcinoma (SCC); 2) assess the association between *MC1R* variants and phenotypic characteristics, including hair and eye color, skin color, skin type, common and atypical nevi, freckles, and solar lentigines; and 3) perform stratified analyses on *MC1R* variants and skin cancer by phenotypic characteristics, and evaluate *MC1R*-phenotype interaction in skin cancer risk.

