**DNA source**				
Blood	24 (62%)	4645 (60%)	2743 (87%)	13304 (89%)
Buccal cells	14 (36%)	3161 (40%)	408 (13%)	1326 (9%)
Tissue	1 (3%)	0	0	245 (2%)

*NMSC* = non melanoma skin cancer.

^a^ healthy subjects are blood donors, friends or relatives of cases.

^b^ individual or frequency.

^c^ includes RFLP, SNaPshot, allele discrimination assay.

We calculated that the minimum required sample size to find a statistically significant association between a *MC1R* variant and melanoma assuming a similar association to that observed in our previous meta-analysis [14] (Odds Ratio (OR) = 1.5) is around 7,500 cases and 7,500 controls for rare variants (1-2% allele frequency in controls), and 1,400 cases and 1,400 controls for common variants (8-10% allele frequency in controls), with 90% statistical power. Sample size for gene-environment interaction analysis was also calculated with the program POWER, version 3.0 [96]. Considering the study of a simple two-way interaction between an environmental factor and a rare *MC1R* variant, around 5,000 cases and 5,000 controls would be needed to observe a multiplicative interaction effect of 2.0, arising to 16,000 cases and 16,000 controls to observe a smaller multiplicative effect of 1.5, both with 90% statistical power. For common *MC1R* variants, the same gene-environment interaction effects of 2.0 and 1.5 could be observed with around 1,200 cases and 1,200 controls, and with around 3,500 cases and 3,500 controls, respectively. Our sample size therefore is appropriate for the purpose of the analysis, and large enough to allow stratified and interaction analyses, especially to find even small interaction effects with the most frequent variants, and larger interaction effects for less common variants.

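### The sample is called large enough for interaction analyses, but for several aim 3 phenotypes the subjects with data fall short of the article's own required sizes

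*Protocol article*

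**What the plan says.** Aim 3 (section The M-SKIP project: rationale and aims) commits the project to stratified analyses by phenotype and to evaluating MC1R-"phenotype interaction in skin cancer risk". Aim 2 names eight phenotypes, "including hair and eye color, skin color, skin type, common and atypical nevi, freckles, and solar lentigines".

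The section Brief description of the collected data and statistical power gives four sizes for a two-way interaction with an environmental factor, at 90% power:

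- common variant, interaction 1.5: "around 3,500 cases and 3,500 controls"
- common variant, interaction 2.0: about 1,200 + 1,200
- rare variant, interaction 2.0: about 5,000 + 5,000
- rare variant, interaction 1.5: about 16,000 + 16,000

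It then concludes that the sample is suitable and "large enough to allow stratified and interaction analyses, especially to find even small interaction effects with the most frequent variants", adding larger interactions for less common variants. The conclusion names no phenotype and no cancer type. Table 1 reports how many subjects have each phenotype recorded.

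**The concern.** The full dataset has 7,806 melanoma cases, 3,151 NMSC cases and 14,875 controls, and against those totals the conclusion looks safe for melanoma. But five of the eight phenotypes are recorded for only 7% to 20% of controls. The section on combining data into a single dataset says that most missing data arise because some studies lack the variable, that imputation or a missing-data indicator would probably introduce bias, and that a two-stage approach is preferred. The missing subjects are therefore not recovered.

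The two parts of the adequacy claim correspond to two of the stated sizes: small interactions with frequent variants (1.5, common) and larger ones with rarer variants (2.0, rare). If the usable sample misses those sizes for some phenotypes, a null interaction for nevi or lentigines could be read as absence of an effect in a study declared able to find even small ones.

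**Working it through.** **Are the stated sizes credible?** Alpha is not stated, so two-sided 0.05 is assumed. A two-proportion calculation for "Odds Ratio (OR) = 1.5" at 90% power, with allele frequency as exposure prevalence, gives 7,400 per group at 1.45% and about 1,400 at 8.5%. Both frequencies lie inside the stated ranges, so the article's 7,500 and 1,400 are reproduced.

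For interactions, the Wald formula for the log interaction odds ratio is

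n per group = (1.96 + 1.28)² × (sum of 1/p over the four control and four case cells) / ln(OR_int)².

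The article gives neither exposure prevalence nor exposure effect. Assuming dominant carriers at allele frequencies of 1.5% and 9%, exposure prevalence 0.3, and gene and exposure odds ratios of 1.5:

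| Variant, interaction | Computed | Stated |
|---|---|---|
| Rare, 2.0 | 5,179 | 5,000 |
| Rare, 1.5 | about 15,720 | 16,000 |
| Common, 2.0 | 1,157 | 1,200 |
| Common, 1.5 | 3,449 | 3,500 |

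Strict reproduction is not possible, but the stated sizes are plausible and are used below as given.

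**What each phenotype can deliver.** Unequal groups are credited through the equal-group equivalent,

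n_eq = 2 × cases × controls / (cases + controls).

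Power is scaled from the stated 90% size n_req:

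power = Φ(3.24 × √(n_eq / n_req) − 1.96).

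Example, solar lentigines in melanoma: n_eq = 2 × 1,419 × 1,088 / 2,507 ≈ 1,232. Against 3,500: 3.24 × √0.352 − 1.96 ≈ −0.04, so power is about 49%.

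Melanoma, counts from Table 1:

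| Phenotype | Cases / controls | n_eq | Common 1.5 (3,500) | Rare 2.0 (5,000) | Common 2.0 (1,200) |
|---|---|---|---|---|---|
| Hair color | 6,841 / 11,889 | 8,685 | >99% | 99% | >99% |
| Eye color | 5,990 / 10,720 | 7,686 | >99% | 98% | >99% |
| Skin type | 6,590 / 4,540 | 5,376 | 98% | 92% | >99% |
| Skin color | 3,517 / 2,963 | 3,216 | 87% | 74% | >99% |
| Freckles | 4,028 / 2,333 | 2,955 | 85% | 70% | >99% |
| Atypical nevi | 2,681 / 1,447 | 1,880 | 66% | 51% | 98% |
| Common nevi | 3,817 / 1,181 | 1,804 | 64% | 49% | 98% |
| Solar lentigines | 1,419 / 1,088 | 1,232 | 49% | 36% | 91% |

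By raw count, skin type also misses 5,000 controls (4,540); it passes the rare-variant size only because its surplus cases are credited.

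**NMSC, common variant, interaction 1.5.** Hair color (n_eq 4,253) and eye color (3,996) pass. The other six do not: skin type has n_eq 2,769 and about 82% power, and the remaining five run from 50% (skin color, 1,292) down to 28% (solar lentigines, 629).

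**The case against.** The strongest reply is that the sizes are borrowed. They were computed for an environmental factor of unstated prevalence and effect, and a phenotype may differ. This stands as a limit on precision. Under the same Wald formula with 10% allele frequency, exposure prevalence 0.4 to 0.5 and exposure odds ratio 1 to 2, the common-variant 1.5 size falls to about 2,900 to 3,150; skin color (3,216) would then pass and freckles (2,955) would sit near the line. At prevalence 0.2 the size rises to about 3,900 to 4,300. The two modest shortfalls therefore depend on inputs that the article does not give. Both nevi variables and lentigines, at 1,880 or less, stay well short across that range. And it is the article that draws its general conclusion on stratified and interaction analyses from these sizes.

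Four stronger readings are tempting, and the article does not support them:

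- *Five phenotypes miss every stated size.* They do not. In melanoma all eight reach about 90% or more for a common-variant interaction of 2.0; by raw count only common nevi (1,181 controls) and lentigines (1,088) fall just under 1,200.
- *Rare-variant main effects are out of reach because no phenotype has 7,500 melanoma cases.* The requirement is "7,500 cases and 7,500 controls for rare variants (1-2% allele frequency in controls", in equal groups. Hair color (8,685) and eye color (7,686) exceed 7,500 once surplus controls are credited. Power within strata depends on the split and the carrier frequency, which are not stated.
- *The powers above are upper bounds.* Case-only studies (2,646 melanoma cases in Table 3), control-only studies (1,464 controls) and between-study variance would lower them, but a different phenotype prevalence could move them either way.
- *A figure is miscalculated.* None is; the fault is an over-general conclusion.

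Table 1 does report availability openly, and the article does confine its rare-variant claim to larger effects. Neither removes the mismatch, because the shortfall for rare variants is shown at that larger effect, 2.0.

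**Conclusion.** The point holds in a limited form. The adequacy sentence is too general for aim 3. For melanoma, five of eight phenotypes fall below 90% power for a common-variant interaction of 1.5: skin color and freckles modestly (87%, 85%), atypical nevi, common nevi and solar lentigines clearly (66%, 64%, 49%). The same five have 36% to 74% for a rare-variant interaction of 2.0. The claim is sound for hair color, eye color and skin type at both, and for all eight at a common-variant interaction of 2.0. For NMSC, six of eight fall short at common-variant 1.5 (28% to 82%).

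These figures assume that phenotypes behave like the environmental factor behind the stated sizes, two-sided alpha of 0.05, cases and controls equally informative per subject, and every subject in Table 1 usable. They do not justify reducing all analyses of the five phenotypes to estimation only, since common-variant interactions of 2.0 remain well powered in melanoma.

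**What to change.** Qualify the sentence by phenotype, variant frequency, effect size and cancer type:

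- Limit the adequacy claim for common-variant 1.5 and rare-variant 2.0 interactions to hair color, eye color and skin type in melanoma.
- Keep the claim for common-variant 2.0 interactions in melanoma, for all eight phenotypes.
- Add a small table of approximate power per phenotype, with NMSC separate. State the assumed alpha, exposure prevalence and exposure effect, and note that case-only and control-only studies and between-study variance would lower the figures.
- State that a null result in an underpowered combination (chiefly nevi and lentigines, and rare variants for all five phenotypes) is not evidence of no interaction.

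The cost is one rewritten sentence, a short table and a less favourable stated power. No new data are needed and no analysis has to be dropped.

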## Statistical analysis plan

### Appropriateness and representativeness of the collected data

Comparability of the main study population characteristics and results between studies included and excluded from the pooled-analysis will be assessed. Funnel plots to evaluate participation bias will be drawn and Egger’s test [97] will be performed.

Departure of genotype frequencies of each *MC1R* variant from expectation under Hardy-Weinberg equilibrium will be assessed by Chi Square test among controls for each study, in order to detect any possible genotyping error or stratification problem in the datasets.

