The main limitation of a pooled analysis, especially with respect to prospective consortia, is that it was planned retrospectively, and hence there was no *a priori* standardization of data collection. On the other hand, pooled-analysis may be feasible with fewer funds than those required for a prospective consortium, and it takes shorter time to obtain results because the original data have already been collected. The quality of genotype methodology may be heterogeneous among different participant laboratories. We will take into account this possible problem both by calculation of Hardy-Weinberg equilibrium and by meta-regression analysis. Finally, while we will try to assess the existence of participation bias, we cannot completely rule out that the results could be affected by the exclusions of the studies from the investigators who refused to participate in this pooled analysis.

In conclusion, the data collected within the M-SKIP project are a valuable resource for investigating associations between *MC1R* variants and skin cancer, particularly for population subgroups, and may be an appropriate setting to better investigate the genetics of sporadic skin cancer. A pooled-analysis of epidemiological studies is feasible, has many advantages over meta-analysis in making it possible to adjust for confounders and assess interactions, and in addition preliminary results may be obtained with lower costs and shorter time than with prospective consortia. We are convinced that its success depends upon the initial definition and approval of clear guidelines necessary for conducting such studies. The diffusion of pooled-analysis in genetic epidemiology field will assist epidemiologists and other health professionals in synthesizing the vast amount of available data on specific gene-disease associations and a common data-base would be the source of possible future investigations.

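### For the 1-2% MC1R variants, the per-study chi-square Hardy-Weinberg test lacks the expected counts it needs in average-sized control groups; an exact test should replace it

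*Protocol article*

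**What the plan says.** Under 'Appropriateness and representativeness of the collected data', the protocol article names the test, the group and the unit. Departure from Hardy-Weinberg equilibrium for each MC1R variant "will be assessed by Chi Square test among controls for each study". The article also gives the purpose of the check, which is made "in order to detect any possible genotyping error or stratification problem in the datasets". It gives no exact alternative and no minimum expected count. It also gives no significance level and no action to follow a departure.

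The Discussion returns to the check when it deals with uneven genotyping quality between laboratories: "We will take into account this possible problem both by calculation of Hardy-Weinberg equilibrium and by meta-regression analysis".

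The allele frequencies come from the sample-size paragraph in 'Brief description of the collected data and statistical power', which separates "rare variants (1-2% allele frequency in controls") from "common variants (8-10% allele frequency in controls"). Control numbers by study design are in Table 3.

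**The concern.** The one-degree-of-freedom chi-square test compares observed with expected genotype counts and needs expected counts that are not tiny. For a rare allele, the expected number of homozygotes is the control number times the squared allele frequency. In a few hundred controls at 1-2%, that is far below one.

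The test then has in effect two outcomes. With no homozygote it cannot flag. With one homozygote, the squared difference is divided by a number near zero and the p-value can become extreme. A sound study could look like a laboratory failure or a stratified sample because one homozygous person was among its controls. This matters because the Hardy-Weinberg check is one of the two tools that the Discussion names for uneven genotyping quality.

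**Working it through.** **Inputs**

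- Allele frequency q of rare variants: 1-2% (sample-size paragraph).
- Controls (Table 3): 6,852 in 21 case-control studies, mean 326; 1,464 in 6 control-only studies, mean 244; 6,559 in one cohort. Without the cohort, (6,852 + 1,464)/27 = 308. Counts per study are not given, so these averages stand in for them.
- Significance level: not stated. Assumed 5% two-sided; 0.1% is shown as a further assumption.

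**The article's own figure.** The only calculated figure that uses the 1-2% input is the main-effect sample size ("Odds Ratio (OR) = 1.5", "with 90% statistical power"). The formula is for two proportions with continuity correction, 1:1, two-sided 5%, with the allele frequency taken as exposure prevalence at mid-range. It gives 7,428 per group at 1.5% (stated: around 7,500) and 1,384 at 9% (stated: 1,400). This supports the allele-frequency input. It has no other bearing on the Hardy-Weinberg test.

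**Expected homozygotes, n × q²**

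- n = 244: 0.02 (1%) to 0.10 (2%)
- n = 308: 0.03 to 0.12
- n = 326: 0.03 to 0.13
- n = 6,559: 0.66 to 2.6

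An expected count of 5 would need 5/q², which is 12,500 controls at 2% and 50,000 at 1%. No study reaches that.

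**Two worked samples.** The statistic is X² = Σ(O − E)²/E. The exact test uses the distribution of homozygotes given the number of variant copies.

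- 308 controls, 1 homozygote and 10 heterozygotes (12 copies, q = 12/616 = 1.95%). Expected counts are 0.117, 11.77 and 296.1. X² = (0.883)²/0.117 + (1.766)²/11.77 + 0.003 = 6.67 + 0.27 + 0.003 = 6.94, p = 0.008. Given 12 copies, the chance of at least one homozygote under equilibrium is 0.10, which is the exact p.
- 326 controls, 1 homozygote and 6 heterozygotes (8 copies, q = 8/652 = 1.23%). Expected counts are 0.049, 7.90 and 318.0. X² = 18.42 + 0.46 + 0.003 = 18.9, p = 0.00001. Exact p = 0.04.

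With no homozygote among 308 controls, the chi-square p is 0.73-0.86 over q = 1-2%, so no flag is possible.

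**Actual size under true equilibrium**, by summing over all allele counts and genotype configurations:

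| n | q | Chi-square size at 5% | Share of those flags with exactly one homozygote | Chi-square size at 0.1% | Exact test size at 5% |
|---|---|---|---|---|---|
| 244 | 1% | 2.4% | 99% | 1.9% | 1.6% |
| 244 | 1.5% | 5.0% | 97% | 2.3% | 1.6% |
| 244 | 2% | 7.1% | 94% | 1.8% | 1.2% |
| 308 | 1% | 3.0% | 98.5% | 2.2% | 1.8% |
| 308 | 1.5% | 6.2% | 96% | 2.2% | 1.5% |
| 308 | 2% | 8.1% | 91% | 1.5% | 1.1% |
| 326 | 1% | 3.2% | 98% | 2.6% | 1.7% |
| 326 | 1.5% | 6.4% | 96% | 2.8% | 1.3% |
| 326 | 2% | 7.7% | 90% | 1.9% | 1.1% |

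**Where the problem stops**

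- At 8-10% and average study size, about 1.6 to 3.3 homozygotes are expected. Chi-square size at 5% is 3.6-4.5%, and single homozygotes do not drive the flags.
- In the 6,559-control cohort at 1-2%, size at 5% is 3.8-4.3%, and one homozygote gives p = 0.31-0.69.

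**The case against.** The strongest reply is that little follows from the error. The article says only that departures are assessed; it does not exclude or down-weight a study because of them. Genotyping method also goes into meta-regression and sensitivity analyses. No effect on a pooled odds ratio can be shown. All of this stands and limits the weight of the point.

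Second, the chi-square test is not far off at 5%: 2.4-8.1% in average-sized studies, sometimes below nominal. The exact test, at 1-2%, is itself conservative for a screen. This stands too. The serious error is in the small p-values. The 1.5-2.8% size at a 0.1% level depends on a threshold that the documents do not contain.

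Third, some single-homozygote flags survive the exact test. The 326-control sample has exact p = 0.04 and is flagged at 5% either way, so sensitivity to one homozygote is partly a property of rare alleles. But the decisions do differ elsewhere: the 308-control sample is flagged by chi-square (0.008) and not by the exact test (0.10).

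Fourth, a full analysis plan could switch to an exact test when counts are low. That softens the point without removing it, since the article names the chi-square test without qualification.

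A reader might infer that the test fails across all 28 studies with controls and all nine named variants. The documents do not support this. The large cohort and the 8-10% variants are not affected in this way. The article does not say how many of the nine variants are rare, nor that every study typed all nine.

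**Conclusion.** The point holds in a limited form. For 1-2% variants in control groups of about 244 to 326, the specified test works in practice as a detector of one homozygote, and its p-values cannot be read at face value.

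This rests on study averages in place of unreported counts per study, on the article's allele-frequency range, and on assumed significance levels. Smaller studies would expect still fewer homozygotes.

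A reader might go further and conclude that the main MC1R results are compromised. Nothing in the article ties a Hardy-Weinberg result to the inclusion or weight of a study, so that conclusion is not supported. This is a minor technical correction to a diagnostic.

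**What to change.** Replace the chi-square test by the exact Hardy-Weinberg test for each variant in the controls of each study, at least wherever the expected number of homozygotes is below 5. Applying it throughout is simpler and avoids a switching rule.

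The cost is a software option; no new data are needed. The small downside is conservatism, with a size of about 1-2% for rare variants at a nominal 5%, so the screen will flag less often.

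Testing separately within ethnic groups should not be part of this change. It does not address small expected counts, and it would remove some of the stratification signal that the article wants the test to detect.

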### Combining data into a single dataset with random effects models

A first analysis using data combined into one dataset, is to fit them with logistic regression models with random slope. Considering a dominant model, let *π*_*ik*_*/X* be the probability of skin cancer for subject *i* (*i = 1,…,n*_*k*_) of study *k* (*k = 1,…,K*) conditional on the presence of a certain *MC1R* variant (*X*). We will account for the fixed *MC1R* effect and the random selection of studies, assuming a model that relates *MC1R* and study effects linearly to the logit of the probabilities:

(3)$$\text{logit}(\pi_{\mathrm{ik}}\text{/ }X)=\alpha +\beta X_{\mathrm{ik}}+b_{k}X_{\mathrm{ik}}$$

In this model the transformed regression coefficient exp(*β*) is the odds of skin cancer for a subject with the *MC1R* variant compared with a subject without the *MC1R* variant, and the *b*_k_ are the study-specific coefficients accounting for the random selection of studies, with *b*_k_ ~ N(0, *σ*^*2*^_*b*_), where *σ*^*2*^_*b*_ represents the between study variance of the *MC1R* effect.

The logistic regression model above described could be applied to different inheritance models and could include covariates, in order to adjust the studied associations by possible confounding factors. In order to include the available information from all the studies, missing values could be estimated in the model with multiple imputation and/or the creation of a missing-data indicator variable. However, when the majority of missing data are the results of non-availability of certain variables in some studies, as for the M-SKIP project, the use of both multiple imputation and the missing-data indicator would be likely to introduce a bias in comparison with the complete case method [98,99] and a two-stage approach would be preferred.

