**Design and methods:**

Based on our experience with the study design of the Melanocortin-1 receptor (*MC1R*) gene, SKin cancer and Phenotypic characteristics (M-SKIP) project, we describe the most important steps in planning and conducting a pooled-analysis of genetic epidemiological studies. We then present the statistical analysis plan that we are going to apply, giving particular attention to methods of analysis recently proposed to account for between-study heterogeneity and to explore the joint contribution of genetic, phenotypic and environmental factors in the development of a disease. Within the M-SKIP project, data on 10,959 skin cancer cases and 14,785 controls from 31 international investigators were checked for quality and recoded for standardization. We first proposed to fit the aggregated data with random-effects logistic regression models. However, for the M-SKIP project, a two-stage analysis will be preferred to overcome the problem regarding the availability of different study covariates. The joint contribution of *MC1R* variants and phenotypic characteristics to skin cancer development will be studied via logic regression modeling.

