### Two-stage analysis with random effects models

The two-stage analysis method [100] will allow us to overcome the problem of the availability of different study covariates. The pooled-estimates of the association of *MC1R* variants with each skin cancer type and each phenotypic characteristic will be calculated as follows.

First, study-specific ORs will be calculated by applying logistic regression to the data from each study to estimate the odds of skin cancer conditional on the presence of a *MC1R* variant (*X*), controlling for confounders *Z*_*k*_. For study *k* (*k = 1,…,K*), assuming just one confounder, the model is written as:

(4)$$\text{logit}(\pi_{\mathrm{ik}}/X)=\alpha_{k}+\beta_{k}X_{\mathrm{ik}}+\gamma_{k}Z_{\mathrm{ik}}$$

where *π*_*ik*_ is the conditional probability of skin cancer for subject *i* (*i = 1,…,n*_*k*_) of study *k*. Although *MC1R* variants were uniformly defined across studies, the confounders *Z*_*k*_ may be specific to a particular study. Analyses with original covariates and with recoded data will be performed and compared. The exposure log-odds ratio for study *k* is denoted *β*_*k*_, the confounding log-odds ratio is denoted *γ*_*k*_, and the *α*_*k*_ are the study-specific intercepts. The *β*_*k*_ are assumed to vary across studies according to the second-stage model:

(5)$$\beta_{k}=\beta +b_{k}+e_{k}$$

where *β* is the pooled-exposure log-odds ratio, *b*_*k*_ are random effects with *b*_k_ ~ N(0, *σ*^*2*^_*b*_), where *σ*^*2*^_*b*_ represents the variability of the study-specific exposure effects *β*_*k*_ about the population mean *β,* and *e*_*k*_ are independent errors with *e*_k_ ~ N(0, *σ*^*2*^_*k*_), where *σ*^*2*^_*k*_ describes the within-study variation of the *β*_*k*_. In the first stage ${\hat{\beta }}_{k}$and its variance ${\hat{\sigma }}_{k}^{2}$ are estimated from equation 4, separately for each study.

The two-stage estimator of the pooled exposure effect *β* is a weighted average of the ${\hat{\beta }}_{k}$, weighted by the inverse marginal variances of the ${\hat{\beta }}_{k}$, denoted $w_{k}={\left({\hat{\sigma }}_{k}^{2}+\sigma_{b}{}^{2}\right)}^{-1}$. Thus:

(6)$$\hat{\beta }=(\sum_{k}w_{k}{\hat{\beta }}_{k})/\sum_{k}w_{k}$$

(7)$$\mathrm{var}(\hat{\beta })={\left(\sum_{k}w_{k}\right)}^{-1}$$

Two methods [100] are frequently used to estimate the random effects variance *σ*^*2*^_*b*_ in equations 6 and 7. These methods are pseudo-maximum likelihood and moment estimation.

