### Joint association of MC1R and phenotypic characteristics with skin cancer risk

Stratified analysis for the association of *MC1R* variants with each skin cancer type will be performed for different phenotypic characteristics. The hypothesis of homogeneity of ORs among strata will be verified using the Breslow-Day test [102].

In order to identify combinations of *MC1R* variants and phenotypic characteristics associated with each skin cancer type, we will perform logic regression, a recently proposed tree-based statistical method intended for binary predictors [103]. This approach is particularly useful for detecting subpopulations at high or low risk of disease, characterized by high-order interactions among covariates, and thus the methodology could be well applied to the study of complex diseases like cancer. First, we will dichotomize continuous and categorical variables by choosing appropriate thresholds and by creation of dummy variables. For phenotypic characteristics we will define dummy variables in order to 1) have as much differentiation as possible in hair and eye color, and 2) separate the extreme classes of skin type and common nevi count from intermediate classes, because it has been suggested [21] that in the meta- and pooled-analysis setting misclassification affects the intermediate classes of exposure more than the extreme ones. Let *X*_*1*_*, X*_*2*_*,…, X*_*p*_ be the binary predictors obtained by dichotomization, and let *Y* be the binary response variable (case/control status). The appropriate logic regression model can be written as:

(8)$$\text{logit}(Y=1|X_{1},X_{2},\ldots ,X_{n})=\alpha +\sum_{j=1}^{k}\beta_{j}L_{j}$$

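### Equations 3 and 8 have one intercept for all studies: the random slope in equation 3 absorbs case:control ratios, and the equation 8 search can be confounded by study

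*Protocol article*

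**What the plan says.** The section on combining data into a single dataset opens: "A first analysis using data combined into one dataset, is to fit them with logistic regression models with random slope". Equation 3 is, in plain notation, logit = alpha + beta·X + b_k·X, where X marks carriage of the variant and k indexes the study. Alpha has no study index. The text says that the variance of b_k "represents the between study variance of the" MC1R effect. Adjustment is optional: the model "could include covariates, in order to adjust the studied associations by possible confounding factors", and study is not named among these.

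In the section on two-stage analysis, equation 4 has alpha_k, which "are the study-specific intercepts". The abstract gives the reason for choosing this route: "However, for the M-SKIP project, a two-stage analysis will be preferred to overcome the problem regarding the availability of different study covariates". The reason is differing covariates, not the intercept.

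In the section on joint association, equation 8 is introduced with "The appropriate logic regression model can be written as" and reads alpha plus a sum of coefficients times Boolean expressions. It has no study index. The same section later says that the risks of the subpopulations found will be estimated by the two-stage method.

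**The concern.** In case-control data the intercept mainly reflects how many cases and controls each study sampled. If those ratios differ and the model has only one intercept, the differences must go elsewhere.

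- **Equation 3.** The only study-indexed term is the carriers' slope. Non-carriers in every study share one log odds, while carriers may differ by study. The sampling ratios therefore enter b_k, its variance no longer has the stated meaning, and beta can be pulled off target.
- **Equation 8.** Nothing is indexed by study. A predictor that is more common in studies with many cases, or in studies with many controls, will look associated with cancer. The predictors are pigmentation variants and pigmentation traits, and the data come from Asia, Australia, three parts of Europe and North America, so frequency differences are plausible. The article does not quantify them.

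At stake are the interpretation of any single-dataset fit, which the Discussion says will be compared and integrated with the other approaches, and the choice of gene-phenotype combinations carried forward under aim 3.

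**Working it through.** The article gives no numerical result for either pooled model, so there is no figure of its own to reproduce. The check uses its counts.

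**Inputs (Table 2, melanoma cases / controls).** Study-level counts are not given, so areas stand in for studies.

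| Area | Cases / controls | Ratio r_k | ln r_k |
|---|---|---|---|
| Australia | 744 / 290 | 2.57 | 0.942 |
| Northern Europe | 858 / 8095 | 0.106 | -2.244 |
| Central Europe | 977 / 2398 | 0.407 | -0.898 |
| Southern Europe | 2747 / 2263 | 1.21 | 0.194 |
| North America | 2480 / 1484 | 1.67 | 0.514 |

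Asia has 0 cases and 345 controls. The cases sum to 7,806, as in Tables 1 and 3 (Table 2 prints 7808, which does not matter here). The range is 2.57 / 0.106, about 24-fold. Table 3 gives 11 case-only studies (2,646 melanomas), 6 control-only studies (1,464 controls) and one cohort (68 melanomas, 6,559 controls).

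**Assumptions.** Carrier frequencies are not in the article. For equation 3 they are set equal in all areas, with no true heterogeneity in the odds ratio.

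**Equation 3 by hand, true OR 1.0.** With equal frequencies and no effect, the log odds of being a case in area k is ln r_k for carriers and non-carriers alike.
- The common intercept is ln(7806 / 14530) = -0.621.
- The mean of ln r_k is (0.942 - 2.244 - 0.898 + 0.194 + 0.514) / 5 = -0.298.
- The model can fit the carriers only with beta near -0.298 + 0.621 = 0.323, so exp(beta) is about 1.38.
- The SD of b_k must be near the SD of ln r_k (divisor 5), which is 1.15. The true SD is 0.

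**Equation 3 by maximum likelihood** (expected counts, integrating over b_k):

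| Setting | True OR 1.0 | True OR 1.5 | Fitted SD (true 0) |
|---|---|---|---|
| Five areas, 10% carriers | 1.37 | 2.06 | 1.14 |
| Five areas, 15% carriers | 1.38 | 2.07 | 1.14 |
| Cohort removed from Northern Europe, 10% carriers | 1.04 | 1.56 | 0.68 |
| Asia added, 15% carriers | 0.71 | 1.00 | 1.89 and 2.02 |

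The third row puts the cohort in Northern Europe, the only area with enough controls to hold it if it lies in a single area. That leaves 858 - 68 = 790 cases and 8095 - 6559 = 1536 controls, a ratio of 0.51. The range falls to 2.57 / 0.407, about 6-fold. In the last row the direction of the bias reverses.

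**Equation 8, one predictor, six areas.** The common-intercept odds ratio comes from the summed 2x2 cells.
- Equal carrier frequency: 1.00 for a true 1.0 and 1.50 for a true 1.5, so no bias.
- Assumed 12% in Northern Europe, 8% in Southern Europe and 10% elsewhere, true OR 1.0: the carriers are 742.8 cases and 1604.1 controls, and the non-carriers 7063.2 and 13270.9. The odds ratio is 742.8 × 13270.9 / (1604.1 × 7063.2) = 0.87. A true 1.5 appears as 1.30.
- North and south swapped: 1.15 and 1.73.

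**With stratification by area** (Mantel-Haenszel, the counterpart of alpha_k), the true value, 1.00 or 1.50, is recovered in every scenario.

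**The case against.** The strongest reply is that neither equation supplies the odds ratios M-SKIP will report. The abstract and the section on two-stage analysis assign the pooled estimates to equations 4-7, which have study intercepts. Combinations found by logic regression are re-estimated the same way, so one that merely marks country would show a within-study odds ratio near 1. All of this stands. A reader might infer that the main MC1R odds ratios are biased, or that aim 3 as a whole fails. The article supports neither: aim 3 also includes stratified analyses with a separate test of homogeneity.

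A reader might also infer that equation 8 always turns sampling ratios into MC1R effects. It does not. With equal frequencies there is no bias, and the direction depends on an assumed gradient.

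The sizes are open to challenge too. Areas are not studies, and most of the odds ratio bias in the five-area fit comes from one cohort, whose ratio nobody chose by design. The article does not say that case-only or control-only studies enter either model, or exactly which data the search uses.

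Three things survive. The spurious SD is still 0.68 without the cohort. Optional covariates do not repair equation 3 unless study is one of them. Two-stage re-estimation cannot recover a combination that a confounded search missed, and the cross-validation and randomization tests mentioned are directed at overfitting, whereas confounding by study can persist across folds.

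**Conclusion.** The concern holds in a limited form and should be fixed before either pooled model is fitted. As printed, equation 3 lacks a study intercept, so for these data its slope variance does not have the stated meaning, and exp(beta) can err upward or downward even when variant frequency is equal everywhere. That follows from the form of the equation and the spread of ratios. The figures (SD 1.14 or 0.68; OR 1.37 or 1.04 for a true 1.0) are illustrations that rest on areas as studies and assumed carrier frequencies. They are not forecasts of M-SKIP results.

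For equation 8 the finding is conditional. Where variant or phenotype frequencies differ between studies, the search is confounded, and combinations may be wrongly picked or missed. Final risks are protected by the two-stage step.

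**What to change.** - **Equation 3:** replace alpha by alpha_k wherever the model is fitted, so that b_k describes only variation in the MC1R effect.
- **Equation 8:** carry study through the search as a forced term or stratum. The article already notes that logic regression works with any properly specified scoring function, so a study-stratified deviance fits its framework.
- **Data:** state that, for cancer outcomes, only studies with both cases and controls inform these two models.

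The cost is a changed symbol in one equation, an added term in the other and one sentence. The downside is that the 11 case-only studies (2,646 melanomas, 34%) and 6 control-only studies (1,464 controls, 10%) drop out of these two models. At most 21 + 1 = 22 studies remain, with 5092 + 68 = 5,160 melanomas and 6852 + 6559 = 13,411 controls. The excluded studies have no within-study odds ratio to contribute. Equations 4-7 need no change.
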